We will use qualitative methods (user-centered design focus groups with clinicians and managers, and interviews with patients and family caregivers) to adapt the QPSS to the unique context of each site and develop protocols for its routine integration in daily practice. For evaluative purposes, we will administer

questionnaires to patients and family caregivers to obtain baseline measurements of their QOL and health care experiences as a pre-intervention comparator group for the outcomes evaluation in stage 2 of the project (Aim 1). In addition, we will collect data about the cost of local adaptation and training (Aim 2).

The current REB amendment pertains to the randomized control trial (RCT) in Stage 2 of the project. The Fraser Health home health offices enrolled included New Westminster, Tri-Cities, White Rock, Gateway, South Delta, and Burnaby (see [Appendix C](#)). Privacy impact assessment has been conducted by the Fraser Health Privacy Office. The project has also obtained approval from Alberta Health Services REB to commence in the Edmonton Zone Home Living sites. Future amendments for research ethics and approval will be submitted for the cost-consequences evaluation and the sustainability (Stage 3) aspects of the project. Island Health sites are withdrawn from the project. They will no longer be enrolled in the project, and no further amendments following the approval for focus group (Stage 1) is required. Sections pertaining to Island Health in version 10 (October 12, 2016) of the protocol are removed from the current protocol. The numbering of all currently approved appendices will remain unchanged.

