## 6 METHODS

### 6.1 Overview of Research Design

The original REB application involved only the focus groups. This amendment pertains to the randomized control trial (RCT) and process evaluation in Stage 2 of the project. The research design for all three stages is briefly described so that it is clear how each stage relates to the overall project. The economic evaluation component of Stage 2 and the sustainability study in Stage 3 will be detailed in a future amendment for research ethics approval.

This project is for the evaluation of both the process of implementing the QPSS into home care practice and the outcomes resulting from it. The use of the QPSS is a complex intervention because it has several interrelated components, presents several challenges for evaluators, and has methodological and practical complications that must be addressed. Adaptation of the intervention to local context and engagement of local health care teams is critical for successful implementation. We will take an action-oriented approach by applying the CIHR Knowledge to Action (KTA) Framework in three stages (see [Appendix 3](#)), and involve clinicians, administrators, patients, and family caregivers in the adaptation and integration of the QPSS into routine practice. We will assess facilitators and barriers to the use of the QPSS find ways of overcoming barriers, implement the QPSS in routine care, evaluate outcomes, and sustain knowledge use.

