### 6.3.4 Allocation to intervention and control conditions

Consenting patients at each home care office will be randomly assigned on a 1-to-1 basis to the intervention or usual care group using a computerized random number generator. Randomization will be stratified by site. To ensure that both members of patient-family caregiver dyad are assigned to the same group, consenting patients will be randomized (whether or not they intend to provide outcome data) and if they have a participating family caregiver, the caregiver will be assigned to the same group. [name], co-PI, is in Montreal and completely removed from the recruitment and allocation process. She will generate and download the randomization sequence, place group allocation on a folded paper inside sequentially numbered opaque envelopes for each site, and mail all envelopes to [name]. She will store a copy of the randomization sequence in a locked filing cabinet in a locked office in Montreal.

The research assistant will inform the research coordinator as soon as a patient (and family caregiver if applicable) is recruited. The coordinator will open the next sequentially numbered allocation envelope to reveal group assignment. She will immediately inform the clinicians in the respective home care office of any patients/family caregivers allocated to the intervention group via generic email notification.

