#### 6.3.8 Quantitative data collection (questionnaires)

All patient participants and family caregiver participants providing outcomes data will complete all the questionnaires at baseline and every two months for a period of one year. Patients will complete: MQOL-E, CANHELP LITE (patient), VR-12 and ESAS-R. Family caregivers will complete: QOLTI-Fv2, CANHELP LITE (family caregiver), VR-12 and CSNAT. The list of questionnaires is in [Appendix 18](#). The Cambian Navigator system will also record detailed usage metrics (frequency and timing of different assessment instruments, time to complete the assessments, viewing of reports).

At baseline, questionnaires will be administered by a research assistant during an in-person meeting at the patient's or family caregiver's home, or via a phone meeting (depending on the participant's preference). Participants have the option of using their own devices, or a project-tablet provided by the researcher assistant during a home visit to complete the questionnaires using the Cambian Navigator application. The questionnaires could be completed independently by the participant or via an interview with the research assistant. If preferred, participants may also choose to return the questionnaires by mail after the meeting. A stamped envelope will be provided. In this case, and in situations where the application is not accessible (e.g., due to poor mobile broadband connectivity), questionnaires will be completed on paper and entered into the Cambian Navigator application on the participant's behalf later on.

Participants will be asked to select any of the following options for completing follow up questionnaires (every two months from start of enrollment for 12 months or until discharge from home care services or death):

- 1) by using their own computer or tablet to access the Cambian Navigator application and complete questionnaire independently,
- 2) with a research staff member via an in-person home visit following the same procedures as above for the baseline questionnaire,
- 3) by having the research staff member administer the questionnaires over the phone,
- 4) by completing the questionnaire independently on paper (to be returned by mail).

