### 6.8.3 Other measures

VR-12 (based on a nearly identical to the SF-12) is a widely-used generic PROM which will be included for the measurement of general physical and mental health status and for cost-effectiveness analysis.

We will also collect patient demographic information including: gender, age, education, employment status, occupation, family income, ethnic background, Canadian-born (or not), religion, diagnoses and date of diagnosis. Family caregivers will be asked to provide their own demographic information including: gender, age, education, employment status, occupation, family income, ethnic background, Canadian-born (or not), religion, living arrangements, relationship to patient.

Please see [Appendix 6](#) for information about reliability and validity of outcome measures, and [Appendix 18](#) for revised QOL questionnaires and outcome measures used in the study.

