## 6.9.3 Analysis of administrative data in cost-effectiveness evaluation

The primary economic evaluation work will involve the comparison of data from stages 1 and 2; the cost-effectiveness evaluation will focus on Stage 2 of the project, running in parallel with, and drawing data from, other components. The framework for the economic analysis will be cost-consequence analysis, where the costs and outcomes of the alternatives are listed separately in a disaggregated format (e.g., intervention costs, hospital costs, clinical benefits, and QOL). As a complement to the cost-consequence analysis, a cost-utility approach will also be employed, with outcomes expressed as quality-adjusted life years (QALYs). The time horizon will be 12 months (consistent with outcomes), and a broad perspective will be adopted to consider both health sector and participant/family costs.

Using health administrative data for each participant, we will determine: (a) frequency and length of use of the QPSS of the home care team, including the number of home care visits and consultations with interdisciplinary team members; and (b) use of other health services, including emergency and acute care admissions. In addition, for the intervention group, the amount of clinician time to use the QPSS and other implementation costs will be captured by the Cambian Coordinator system). The dollar value of resources will be determined using local Fraser Health accounts data, supplemented using the Canadian Institutes of Health Information patient cost estimator for acute sector admissions ([www.cihi.ca](http://www.cihi.ca)).

Bootstrapping will be used for comparison of the mean costs and QALYs between groups, with non-parametric confidence intervals, and to estimate the incremental cost-utility ratio. The bootstrapped cost-effect pairs can graphically be represented on a cost-effectiveness plane, and cost-effectiveness acceptability curves calculated, showing the probability that an intervention is cost-effective at a specific threshold ratio. This information will be used to evaluate relative cost for each of the groups and ascertain whether QPSS implementation results in cost-saving or expense.

A data access request will be submitted to identify the specific data elements that will be used for the study.

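### Section 6.9.3 names no baseline VR-12 utility or office adjustment for the QALY comparison, a precision gain available from data already collected (low severity)

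*Protocol*

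**What the plan says.** Protocol section 6.9.3 sets out the economic comparison in one sentence: "Bootstrapping will be used for comparison of the mean costs and QALYs between groups, with non-parametric confidence intervals, and to estimate the incremental cost-utility ratio". The resampled cost-effect pairs then feed a cost-effectiveness plane and acceptability curves. No covariate is named, and nothing is said about resampling within offices.

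The material for an adjusted analysis is already in the design:

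- Section 6.8.3 says that VR-12 "will be included for the measurement of general physical and mental health status and for cost-effectiveness analysis".
- Section 6.3.8 fixes its timing: "All patient participants and family caregiver participants providing outcomes data will complete all the questionnaires at baseline and every two months for a period of" (12 months).
- Section 6.3.4 states: "Randomization will be stratified by site".

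Two statements limit the weight of the point. Section 6.9.3 gives the analysis a supporting role: "As a complement to the cost-consequence analysis, a cost-utility approach will also be employed". Section 6.1 says: "The economic evaluation component of Stage 2 and the sustainability study in Stage 3 will be detailed in a future amendment for research ethics approval". The summary in section 2 repeats the deferral: "Future amendments for research ethics and approval will be submitted for the cost-consequences evaluation".

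**The concern.** A 12-month QALY is the area under a participant's own utility curve. If the curve starts at the baseline value, baseline utility enters the QALY directly, and it enters again through its correlation with later scores. When the arms differ by chance at baseline, part of that difference passes into the incremental QALY. Bootstrapping unadjusted means describes this variation correctly but does not reduce it.

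The contrast with section 6.9.2 makes the omission visible. There the protocol names analysis of covariance and takes account of home care office, but only for quality of life and care experience. Nothing extends that model to QALYs or costs, so an analyst following 6.9.3 as written would compare unadjusted means.

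Precision is what is at stake. The incremental QALY is the denominator of the cost-utility ratio and one axis of the plane. If it is small, a ratio built on it is sensitive to small movements.

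**Working it through.** **No figure to reproduce.** The protocol states no utility SD, no baseline-QALY correlation, and no target difference or power for QALYs. Its 432 and 158 in section 6.9.2.1 belong to the clinical outcomes. They reproduce as a three-group F test with assumed 80% power and Cohen's f of 0.15 and 0.25, but have no bearing here.

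**Inputs.** From the protocol: 180 participants per arm (6.9.2.1), 1:1 allocation stratified by site (6.3.4), and VR-12 at baseline and every two months for a year (6.3.8). Assumed: baseline-QALY correlation ρ of 0.3, 0.5 or 0.7, and utility SD of 0.10 to 0.15.

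**Step 1: precision.** The adjusted-to-unadjusted ratio of standard errors is √(1 − ρ²).

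| ρ | Variance ratio, 1 − ρ² | SE ratio | Interval narrower by |
|---|---|---|---|
| 0.3 | 0.91 | 0.954 | about 5% |
| 0.5 | 0.75 | 0.866 | about 13% |
| 0.7 | 0.51 | 0.714 | about 29% |

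**Step 2: check by simulation.** This used 5,000 trials, 180 per arm, SD 0.15 and a true difference of zero. The mean estimate was about 0.000 with and without adjustment, so neither is biased. The SE fell from 0.0159 to 0.0138 at ρ = 0.5 (ratio 0.87), and from 0.0157 to 0.0112 at ρ = 0.7 (ratio 0.71). Both agree with step 1.

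**Step 3: chance imbalance at baseline.** The SE of the baseline difference is SD × √(2/180) = SD × 0.1054. That is 0.0105 for SD 0.10 and 0.0158 for SD 0.15. The probability of a difference larger than 0.01 in either direction is 0.34 and 0.53 respectively.

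**Step 4: how much carries over.** The carry-over is a regression slope, not a correlation. Assume seven equally spaced visits (baseline plus six), equal SDs, a constant between-visit correlation r, and the trapezoid rule. The two end visits have weight 1/12 each and the five inner visits 1/6 each.

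- Slope = 1/12 + (11/12)r, which is 0.45 at r = 0.4 and 0.63 at r = 0.6.
- QALY variance in units of SD² = r + (1 − r) × (2/144 + 5/36) = r + 0.1528(1 − r), which is 0.492 and 0.661.
- Implied ρ = slope/√variance = 0.45/0.701 = 0.64 and 0.633/0.813 = 0.78.

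A one-SE imbalance would therefore move an unadjusted incremental QALY by 0.45 × 0.0105 = 0.005 to 0.63 × 0.0158 = 0.010.

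**Step 5: limits of this model.** It ignores death and discharge, at which section 6.3.8 ends follow-up. In this population both would add variation to 12-month QALYs and dilute ρ below 0.64 to 0.78, so the range down to 0.3 must be kept.

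**The case against.** The strongest reply is that the section rules nothing out. A reader might infer that the protocol commits to raw means and rejects adjustment. The documents do not support that: neither the word raw nor unadjusted appears, bootstrapping is a resampling device, and a regression fitted within each replicate would still satisfy the sentence. The economic detail is also expressly left to a later amendment. Both parts stand. What remains is that a contrast and its outputs are already written without adjustment, whereas 6.9.2 spells adjustment out for the clinical outcomes. The amendment would start from this text.

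A reader might also infer that the unadjusted comparison is biased. It is not. Chance imbalance is ordinary sampling error, and the bootstrap interval already reflects it. The case for adjustment is efficiency and a single-trial estimate less dependent on that imbalance.

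A third inference would be that adjustment raises power by some stated amount. Section 6.9.3 plans intervals, a plane and acceptability curves, with no economic power target, so no power claim applies.

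Finally, office adds little to the point. Randomisation within site already limits imbalance between offices. Including office aligns the analysis with the design, but the gain comes mainly from baseline utility.

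**Conclusion.** The point holds as an inexpensive improvement of low severity. It is not an error in the protocol. As written, 6.9.3 describes a valid and unbiased comparison that is less precise than the collected data allow. The likely gain is a QALY interval narrower by about 5% to 29%, for baseline-QALY correlations of 0.3 to 0.7. These correlations are assumptions. Deaths and discharges could place the true value at the lower end, where the gain is slight. None of the four hypotheses in section 5 depends on this analysis.

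**What to change.** In section 6.9.3, or in the economic amendment already promised, state the following:

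- Resample participants within office and arm, keeping each participant's cost and QALY together.
- In each replicate, estimate the incremental QALY by regression on arm, baseline VR-12 utility and office, and the incremental cost by regression on arm and office.
- Use these estimates for the cost-utility ratio, the cost-effectiveness plane and the acceptability curve.
- Report the unadjusted mean differences as a sensitivity analysis.

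The cost is one or two sentences and two regressions per replicate, with no new data, visits or participants. The small downside is that any missing baseline VR-12 needs a simple imputation, which should be named in the same place.

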## **6.10 Potential Benefits**

Some patient and family caregiver participants in our earlier catalyst projects reported that completing the outcome questionnaires stimulated them to reflect on their various areas of their life and care, or normalized how they were feeling, which they found helpful. They may also benefit from the opportunity to potentially improve services to others in their situation.

Clinician participants may not derive any particular benefit from participation in the study; however, they may appreciate the opportunity to have a voice in the development of protocol for implementation of the tablet system into practice. Clinician participants may also be able to gain empowerment from being involved in the development of integrated care for people with life-limiting illness while simultaneously having the opportunity to develop educative-research skills that can support knowledge translation. The clinicians will also gain knowledge and better understanding of the application of the QPSS through the hands-on practice of using the system.

## **6.11 Potential Risks**

### **6.11.1 Patients and family caregivers**

Potential patient and family caregiver participants will be advised that their participation is strictly voluntary and that their decision to participate or not in the study will not compromise the care they are receiving. They will also be advised that they may refuse to answer any questions or withdraw participation in the project at any time. Care providers will be able to see the information from clients and family caregivers about their experiences with care. The intent is for care providers to use this information to provide better care.

### **6.11.2 Clinicians**

No potential for harm is anticipated for clinician participants. Participation in the project will not affect their employment status in any way and their workplace performance will not be evaluated in any way. Clinicians at participating home care offices who choose not to participate will not be affected in any way. Clinician participants will be reminded their participation is voluntary and that they will be able to withdraw from the project at any time without needing to provide an explanation or reason. Any

managers or colleagues who are members of the research team will not have access to any focus group or interview data that includes identifying information.

We recognize that focus group participants may be in supervisor-subordinate relationships, and that participants may not feel free to share all their perspectives as a result. However, the goal is not so much about all the different perspectives but rather about coming to an agreement on adaptations required and how to implement the QPSS in practice. Prior to data collection, participants are reminded that the goal of the focus group is to discuss ways of using the QPSS as fitting with their practice setting, to arrive at an agreed plan that reflects front-line clinicians' and managers' perspectives on the integration of the QPSS in practice.

#### **6.12 Incidental findings**

In the event a patient or family caregiver participant has very strong dissatisfaction of care, or is found to be in poor mental health during a phone interview, the research personnel involved in data collection are trained to respond as follows:

- Be empathetic towards the participant's frustrations.
- Explain that the research personnel is a part of Trinity Western University / University of Alberta and suggest that the individual contact Fraser Health ([[contact]](mailto:[contact])) or Alberta Health Services to discuss their concerns, so that the issues could be appropriately conveyed to the healthcare administration.
- Ask the participant how he/she can be supported, and provide contacts to the appropriate non-profit agency for support and direction to the participant.
- Reschedule the phone interview, if the participant wishes to do so.
- Inform the project coordinator of the incidental finding.

#### **6.13 Subject Safety Provisions**

If the patients and family caregivers disclose thoughts of harm to oneself or to others during the course of the data collection, the research staff is required by law to report the information to the treating team in order to allow for appropriate treatment and follow-up.

Data collection will be stopped at any time upon request by the participants. The provisions for termination of data collection are specified in all participant consent forms.

#### **6.14 Data Security and Protection of Privacy**

##### **6.14.1 Focus group (clinician) and interview (clinician, patient, family caregiver) data**

Given the location of the focus groups, there are limits to confidentiality regarding clinician participant attendance. By the nature of focus groups, researchers will be aware of the identities of participants in the clinician focus groups. This information will be kept confidential and will not be accessible to anyone outside of the research team. Participants within each focus group will be aware of each other's' identities and of the data provided. At the start of the focus group, we ask that all participants refrain from using names or identifying details of their patients and to be considerate of the privacy of the other participants in the focus group. We further ask that participants do not share what was discussed at the focus group, content and names, with those outside the group. Identities of the participants will be kept confidential and will not be accessible to anyone outside of the research team.

The focus groups (clinicians) and interviews (clinicians, patients, family caregivers) will be digitally audio-recorded and the audio files subsequently transferred from the recording device to a password protected and encrypted computer. The digital recording will then be submitted by the Principal Investigator (PI) or

the research staff to a transcription service (<https://www.pointswesttranscription.com/>) via a secure link provided by the service. The focus group and interview data will be anonymized during transcription. Transcriptions will be returned via a secure password-protected link. Please see Appendix 21 confirming the confidentiality agreement with the transcription service. This is the same service that has been used for previous Fraser Health research projects. Identifiable information of participants will only be accessible to the PI, Co-Investigators (CIs), research staff and transcriptionist(s). All staff will be made aware of their responsibilities concerning privacy and confidentiality by the PI and CIs.

